## Abstract

**Background:**

Long-term care in Germany lags behind other countries, when it comes to adopting scientific knowledge into daily practice and vice versa. Structures for transferring technological innovations from science into practice or organizational development in nursing homes are missing, although comparable structures in the medical sector exist. Ensuring high-quality care remains one of the key challenges for the future in Germany, which can only be met by creating and implementing such transfer structures in the form of the “Transfer Cluster of Academic Teaching Nursing Homes” in order to make working in long-term care more attractive.

**Methods:**

The aim of the Transfer Cluster is (a) implementing three Academic Teaching Nursing Homes in Bremen with (b) a nationwide rollout after nine years. An explanatory sequential mixed-methods design with an embedded quasi-experimental long-term study is used for the evaluation of the “Transfer Cluster of Academic Teaching Nursing Homes” initiative. In three nursing homes, different elements of the Transfer Cluster (e.g., digitalization) will be implemented and evaluated (intervention group). The main outcomes of the summative evaluation are job satisfaction of employees and quality of care of residents. The formative evaluation includes research diaries and focus groups. Results will be compared with three matched nursing homes as a control group. Dissemination material will be developed and a concept for the nationwide rollout will be derived.

**Discussion:**

Long-term care faces different challenges in the next years, including the realization and connectivity to research, especially to digitalization and the growing decline in staff. The close exchange with employees of the Academic Teaching Nursing Homes and their management provides important insights into everyday practice and leads to development of innovations which are really needed and therefore more accepted by employees and are tailored to their working conditions. Clear strength of the “Transfer Cluster of Academic Teaching Nursing Homes” initiative is the duration of up to nine years and a nationwide rollout which is thought of from the beginning. A successful nationwide rollout of Academic Teaching Nursing Homes will be a great milestone in nursing science and practice.

**Trial registration:**

German Clinical Trials Register DRKS00035292 (Date of registration: December 9, 2024).

**Supplementary Information:**

The online version contains supplementary material available at 10.1186/s12912-026-04325-4.

## Introduction

Long-term care (LTC) in Germany lags behind other countries, e.g., the Netherlands or the USA, when it comes to structures that combine science, teaching and care itself. This leads to the fact that transferring innovations from science into practice or organizational development in nursing homes takes too much time [1–3]. This may be related to the fact that professionalization and academization of care came up late in Germany when compared to the Netherlands or the USA, and scientific culture and structures in LTC are in the process of construction [4]. Further ongoing challenges for nursing homes such as technological and other related health innovations and aggregated care needs are also present in everyday care [1].

To face these ongoing challenges and to enable the implementation of technological, social and organizational innovations in everyday care situations, it is essential to create transfer structures in LTC. In the medical sector, university hospitals and academic teaching hospitals offer the opportunity to carry out teaching and research directly in everyday health care. This provides a direct transfer path from research via teaching to healthcare – and vice versa, impulses from healthcare practice flow back into research and teaching. Internationally, similar concepts such as the *Living Lab in Ageing and Long-Term Care* in the Netherlands [5, 6] or the *Teaching Nursing Homes* in the USA and Norway [7, 8] have been established in LTC for more than 25 years.

These concepts are described as a possible perspective for improving the transfer and quality of care in Germany [9]. Additionally, there are initial concepts for nursing homes in the project *Nursing Practice and Science in the Care of People with Dementia in Long-Term Care through the Dementia Living Lab Approach* (PraWiDem), which, however, relates to people with dementia only and also has a limited duration of just three years [10]. A comprehensive concept for LTC is still missing, although such a “transfer structure” would also be important in Germany and would constitute a crucial component for ensuring high-quality LTC.

The innovative core idea of the “Transfer Cluster of Academic Teaching Nursing Homes”^1^ initiative is to create a Cluster of Academic Teaching Nursing Homes in order to reconcile research, teaching, and daily care-giving, and thus enabling a two-way transfer. The TCALL initiative, funded up to nine years by the Federal Ministry of Research, Technology and Space, aims to build a foundation for a new, continuously science-based care culture in LTC. In the first phase of TCALL, three nursing homes will be restructured into Academic Teaching Nursing Homes (ATNH). Subsequently, this structure will also be rolled out, first to the federal state of Bremen and finally to Germany. TCALL contributes to strengthening LTC proactively in the field of education and training, care quality, and job satisfaction by providing a space for sustainable innovation structure and culture. This newly created space allows to identify, test, and subsequently implement innovations into everyday LTC, which have been evaluated positively before. As TCALL also aims to disseminate the established structures widely in Germany before the initiative ends, TCALL has a significant scientific and societal impact, particularly when considering the recent challenges in LTC. The TCALL initiative will develop approaches to ensure best LTC in the future and to address general societal challenges such as demographic change as well as upcoming challenges like robotics and artificial intelligence (AI) [11].

## Background

### Situation in Germany

Ensuring high-quality care remains one of the central challenges of the future in Germany, which can only be met by creating transfer structures between science and practice in order to make LTC more attractive. This includes improved working conditions, introducing technological innovations across LTC, and adapting internal workflows in LTC through human resources development and organizational development, as well as continuing education and training content and structures. However, there are currently no effective and sustainable structures to support nursing homes in implementing the necessary organizational and technological innovations. On the one hand, nursing homes in Germany have not yet established a consistent scientific culture, including appropriate continuing education structures. This is because training as a nurse is nonacademic in Germany and nursing homes do not have a cooperation with universities so far. On the other hand, knowledge about their acceptance, effectiveness, and efficiency is still limited, although technological innovations have been promoted for many years [12, 13]. Another fact is that science usually has not a direct access to nursing homes and the real working conditions. This might lead to asking the wrong questions for researchers and providers who focus on the development of technological innovations that do not solve the real-world problems in LTC. Therefore, implementing successful innovations in standard care rarely succeeds and the process is lengthy [2, 3]. Various studies show that evaluations under laboratory conditions and the establishment of showrooms with technical solutions for practical transfer alone are not sufficient, as there is a lack of high-quality evaluations [12, 13] and the development of innovations often bypasses practical needs [14]. In addition, the participatory involvement of care-givers is often lacking, which is an important condition for integrating innovations into daily routines [15]. Also the legal framework does neither provide refinancing for the introduction of digital care innovations nor for follow-up costs [16]. Human resources and organizational development processes also require long-term testing and continuous development in nursing homes under real conditions. Besides these facts, the demographic change is ongoing while the number of employees in care continues to decrease [17] which carries a risk for decreasing quality in caring.

### Aims and structure of the TCALL initiative

The TCALL initiative is funded up to nine years by the German Federal Ministry of Research, Technology and Space and is a cooperation between the University of Bremen, the City University of Applied Science Bremen, the Integrated Health Campus Bremen and three nursing homes as practical partners (one from Johanniter and two from Caritas^2^). TCALL combines various sub-projects to achieve the vision of a Transfer Cluster of Academic Teaching Nursing Homes. This vision aims to create a direct transfer pathway from research via training to care – and vice versa, from care practice and the identification of problems back to research and training which address these problems. This is achieved by introducing innovations (social and technological) into LTC across the board and adapting internal work processes in LTC accordingly through personnel and organizational development, as well as further developed training content and structures. TCALL offers the opportunity to implement innovations directly in everyday care in the ATNH, which is not possible in conventional research projects and under laboratory conditions. These real-life conditions will also lead to feedback loop effects for science so that new and relevant research questions can be derived and tackled. In order to support these processes, special staff was hired and introduced in the three ATNH. These transformation and innovation agents (TIAs)^3^ are a special feature in the TCALL initiative, and they are responsible for a regular exchange between nursing homes and research partners. The TIAs form the interface to the ATNH and ensure a trustful cooperation. They will support all measures within TCALL to ensure that processes run smoothly and to reduce the workload of employees in the participating nursing homes.

In summary, TCALL aims at a double innovation structure: Firstly, the diverse technical, social and organizational innovations will be participatory selected, tested in one ATNH, evaluated, and implemented in the whole Cluster of Academic Teaching Nursing Homes. Subsequently these innovations will be prepared for transfer into other nursing homes. This applied transfer pathway (Fig. 1) is based on a framework for evaluating technical innovations in LTC [18–20]. Secondly, a transfer structure will be created enabling recursive feedback between the nursing homes, the innovators and later the regulatory authorities, the mutual and joint development and implementation of new technical products and organizational structures. In this way, the TCALL initiative contributes to improving the quality of care and working conditions in the LTC sector and to achieving financial sustainability for the ATNH, by bringing together all stakeholders involved in the provision of LTC.

**Fig. 1 Fig1:**
[figure not shown]
Transfer path of TCALL

After a phase of planning and preparation in 2023 (start-up phase), the first sub-projects started in December 2023 and January 2024. The first one (Development of a decentralized learning infrastructure) aims to design and develop a learning infrastructure for LTC close to the workplace including a combination of different learning concepts. The second (Center for Coordination and Transfer), which is the subject of this study protocol, is responsible for the overall evaluation, strategic steering and dissemination of the entire TCALL initiative as well as for the development of strategies for a nationwide rollout.

Two more sub-projects started in 2024: “Digitalization and transfer of technical innovations in LTC” aims to select and test digital technologies, while “Competence-oriented work-organization” aims to implement new organizational and personnel structures in nursing homes based on the qualification levels of the employees. The objective of “Evidence-based Nursing” is the establishment of developed instruments and measures in the context of evidence-based nursing in participatory cooperation with the ATNH and is planned for the end of 2025. The timetable for all sub-projects in TCALL until the end of 2027 can be seen in Fig. 2.

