#### Data collection

The study protocol follows the SPIRIT reporting guidelines for study protocols for clinical trials. Outcomes will be measured with reliable, valid and pretested instruments (Table 1). Most used questionnaires are free to use and do not need any license except for “The Neuropsychiatric Inventory Nursing Home Version (NPI-NH)” and the *“*Adult Social Care Outcomes Toolkit (ASCOT-SCT4)”. Licenses in both cases were obtained and permission for use is confirmed. Ethical approval was confirmed by the ethics committee of the German Society of Nursing Science in October 4th, 2024. Baseline data collection in the intervention group started in November 11th, 2024 and is ongoing, follow-up data collection continues at six-month intervals, and the end of the first study phase is planned for 2027. Questionnaires for employees and residents are completed digitally, with the exception of the Adult Social Care Outcomes Toolkit (ASCOT-SCT4) [21], which is paper-based. Data collection of residents’ files, structural data of institutions and data from quality audits will be retrieved by the staff of the University of Bremen and the City University of Applied Sciences in Bremen. All data collection will take place in the intervention nursing homes and matched control groups. Data analysis is pseudonymized.

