#### Summative evaluation

As briefly described above, the evaluation focuses on different outcomes at two different levels: (i) employees and (ii) residents, but on non-intended effects as well. Changes due to the complex intervention are expected in job satisfaction of employees in the ATNH compared to control nursing homes. Additionally, there are several changes expected for employees concerning organizational commitment, mental workload or sickness rates and the use of temporary employment agencies. For residents it is expected that the complex intervention will alter quality of care in the ATNH compared to control nursing homes. Further outcomes include the number of nursing home-sensitive hospital diagnoses and apathy symptoms. A full list of all outcomes and instruments is shown in Table 1. All outcomes are measured at baseline, at multiple follow-ups at six-month intervals and at the end of the study (in this case the end of the first phase in 2027). Outcomes are measured via (standardized) questionnaires and/or external assessment by a nurse, and an analysis of resident files and routine data of nursing homes. Sociodemographic data of employees and residents will be collected and analyzed. A secondary data analysis of obligatory quality indicators and external quality audits will be conducted. These internal and external quality indicators (see supplementary material additional file 1) are mandatory in Germany since 2022 and are reported publicly semi-annually. Internal quality indicators include 15 self-assessed items regarding three themes collected by nursing homes and their employees. External quality audits are structured in six themes with 24 items and are collected from assessors and evaluators on behalf of the LTC insurance fund (e.g., Medizinische Dienste/medicproof GmbH).

**Table 1 Tab1:** Overview of outcome and instruments for employees and residents

Outcome	Instruments (Source)

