###### Indicators of a high workload

Due to the complex organizational change in staff, changes in indicators for a high workload, like sickness rate, staff turnover and the use of temporary employment agencies are expected at end of the study. To some extent, it is possible that during the restructuring process of staff deployment and shortly after implementation, the indicators for a high workload show an increase instead of a decrease. These non-intended effects are based on the fact that learning and getting used to new workflows initially leads to additional work and only later to positive effects (J-curve effect).

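### The protocol does not establish that t0 precedes the intervention, yet t0 is the only reference point of the difference-in-difference

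*Protocol article*

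**What the plan says.** **Sub-project starts** (Aims and structure of the TCALL initiative, text after Fig. 1). "the first sub-projects started in December 2023 and January 2024". One of these "aims to design and develop a learning infrastructure for LTC close to the workplace". The other is the Center for Coordination and Transfer, which "is responsible for the overall evaluation, strategic steering and dissemination of the entire TCALL initiative". The same text adds: "Two more sub-projects started in 2024". These are digitalization and competence-oriented work-organization, the latter meant to bring in new organizational and personnel structures. Their months are not given.

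**TIAs** (same section). To support the process, "special staff was hired and introduced in the three ATNH". No date is given. Health economic evaluation counts TIA costs on the intervention side, apart from study costs.

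**Baseline.** Data collection states: "Baseline data collection in the intervention group started in November 11th, 2024 and is ongoing". Trial status confirms that t0 was still open at submission, with control homes still being recruited.

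**Analysis.** Statistical analysis compares t0 with t1 to t6 and asks whether the changes differ between intervention and control groups, as a difference-in-difference. No earlier reference is named.

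**Expected early course** (Indicators of a high workload). Sickness rate, turnover and agency use may rise during restructuring and shortly after implementation, because "learning and getting used to new workflows initially leads to additional work and only later to positive effects (J-curve effect").

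**Earlier data.** According to Summative evaluation, the internal and external quality indicators "are mandatory in Germany since 2022 and are reported publicly semi-annually". Quality of care in nursing homes notes that the homes collect their routine data regardless of the study.

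**The concern.** A difference-in-difference estimates the effect of an initiative only if the reference wave is untouched by it. Here sub-projects had been starting for most of a year before the first baseline questionnaire. One of the 2024 sub-projects concerns staffing structures, and the TIAs had been placed in the homes at some point before the article was written. The protocol also describes a mechanism by which early implementation can make some outcomes temporarily worse.

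If t0 falls in such a period in the intervention homes, recovery from a disruption caused by the initiative would be reported as benefit. If some lasting benefit had already arrived, it would be built into the baseline and lost from the estimate. With one reference wave the design cannot tell these cases apart, and parallel trends cannot be examined. Both main outcomes, job satisfaction and quality of care, use this reference, and the evaluation is meant to justify continuing the initiative. Strengths and limitations does not raise the point.

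**Working it through.** The plan gives no figure of its own to reproduce. The check has four steps.

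**1. Gap from sub-project start to baseline opening.** Months = days to 11 November 2024 ÷ 30.44.

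- Start 1 December 2023: 346 days, 11.4 months
- Start 31 December 2023: 316 days, 10.4 months
- Start 1 January 2024: 315 days, 10.3 months
- Start 31 January 2024: 285 days, 9.4 months

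The gap is 9.4 to 11.4 months. Baseline data collected after the opening day lie further out. Six steps of six months from November 2024 put t6 at November 2027, which agrees with the stated end of the first phase.

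**2. What the gap measures.** It runs from project start to baseline, not from first exposure in a home to baseline. The possible exposures at t0 are:

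- Coordination and evaluation centre: not a care intervention.
- Learning infrastructure: began with design and development; no date of use in the homes.
- Digitalization: selects and tests technologies; started in 2024, month not given.
- Competence-oriented work-organization: changes staffing structures; started in 2024, month not given.
- TIAs: part of the intervention by the protocol's own costing; in the homes, date not given.

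Exposure at t0 is therefore plausible for the TIAs and for work-organization, but it is not dated for any element.

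**3. Effect on the estimate.** Score outcomes so that higher is better. Let Δ be the true effect at follow-up, I the intervention homes and C the control homes:

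estimate = (I at follow-up − I at t0) − (C at follow-up − C at t0)

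- If the intervention homes sit d below their undisturbed level at t0, have recovered by follow-up, and the controls are unaffected: estimate = Δ + d.
- If a lasting gain g is already present at t0: estimate = Δ − g.

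The document gives neither d nor g, so these values are assumptions. On the 1-to-7 job satisfaction item with Δ = 0, a dip of 0.1, 0.3 or 0.5 points yields an apparent benefit of 0.1, 0.3 or 0.5. With Δ = 0.3 and d = 0.3, the estimate is 0.6. If a quarter of the effect is already present (g = 0.25Δ), the estimate is 0.75Δ.

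**4. Earlier data that could exist.** Half-yearly public reporting in 2022 and 2023 gives at most 2 × 2 = 4 points. If reports follow calendar half-years, the second half of 2023 includes December, which leaves 3 points wholly before the first start. Four points allow three half-year changes before the start, and three points allow two. With t0 alone there are none.

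**The case against.** The strongest reply is that start dates of funded sub-projects are not dates of change in the homes. The evaluation centre has to exist before a baseline can be collected, and the learning infrastructure began with design. Innovations are to be tested in one home before they reach the others, and the abstract and introduction describe implementation and restructuring as still to come. The sub-project timetable is in Fig. 2, which was not available for this review and may settle some dates. This stands. A reader might infer that t0 is certainly not a pre-intervention measurement; the documents do not support that.

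The J-curve is also narrower than it may look. The protocol calls the early rise possible to some extent, and only for sickness rate, turnover and agency use. A reader might infer a predicted dip in job satisfaction or quality of care; the text predicts none. A link through workload is plausible, but it is inference.

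Pre-trend checks and look-back windows may be left to an analysis plan that is not shown. That is fair as to detail. The point here rests on what the article itself fixes: t0 as the reference, its opening date, and TIAs already in place. For questionnaire outcomes no later document can supply a missing earlier wave.

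Finally, retrieving files of residents who have since left or died may be barred because participation rests on written consent. This limits the remedy to public indicators and home-level aggregates, which do not need individual consent.

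**Conclusion.** The concern holds in limited form. The protocol does not establish that t0 precedes the intervention, and its own dates suggest that for some elements, chiefly the TIAs and possibly work-organization, it may not. Baseline opened 9.4 to 11.4 months after the first two sub-project starts, but how much of that time involved exposure in the homes is not stated.

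Any bias passes one-for-one into the estimate: upward for a dip that has resolved, downward for a lasting early gain. Neither size nor direction can be derived from the document. The algebra assumes that the control homes are undisturbed at their own t0 and, for the upward case, that the dip has passed by follow-up.

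The matter is worth settling before analysis. For quality of care and the workload indicators, an earlier reference appears obtainable at low cost. For job satisfaction it is not, so what remains is the wording of the claim.

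**What to change.** 1. State, for each home, the date on which each element (TIAs, learning infrastructure, digital technologies, work-organization) took effect relative to that home's t0.
2. For the publicly reported quality indicators, add the half-years before December 2023 in all six homes as the pre-period. Do the same for the home-level routine data (sickness rate, turnover, agency use and adverse-event counts) where the homes can supply them as aggregates.
3. On these outcomes, check pre-trends and show effects by half-year, keeping t0 as a separate wave. With three homes per group the pre-trend check will be largely descriptive and should be presented that way.
4. For questionnaire outcomes, which have no earlier data, report which elements were active in each home at t0. Where any were, limit the conclusion to change since t0. Where none were, say so and keep the present interpretation.

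Cost: some retrospective extraction, possible gaps in older routine data (particularly in control homes not yet recruited), and a more modest claim for job satisfaction. No further burden falls on residents or employees as respondents.
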